## Abstract

**Aims:**

End‐stage cancer may resemble a heart failure (HF)‐like phenotype marked by cardiac wasting, dysfunction, and symptoms such as dyspnoea, congestion, and impaired physical function. The EMPATICC (EMPower the heArt of patients with TermInal Cancer using Cardiac medicines) trial evaluates the safety and efficacy of optimized HF therapy in patients with advanced cancer to improve self‐care ability.

**Methods:**

EMPATICC is a multicentre, investigator‐initiated, randomized, double‐blind, controlled, proof‐of‐concept trial employing a joint cardio‐oncology care approach. Patients were randomized 1:1 to optimized HF therapy (sacubitril/valsartan, empagliflozin, ivabradine, ferric carboxymaltose) plus usual care, or usual care alone, for 30 days, followed by a 30‐day open‐label extension. Eligible patients had stage IV solid tumours (per Union for International Cancer Control), were receiving palliative care, had a 1–6 month life expectancy, and were on optimized analgesia. At baseline, first patients had to meet ≥2 criteria of the following indicating cardiovascular risk: heart rate ≥70 bpm, N‐terminal pro‐B‐type natriuretic peptide ≥600 pg/ml, elevated high‐sensitivity troponin, left ventricular ejection fraction <55%, left ventricular mass loss >15%, transferrin saturation <20%, or moderate/high likelihood of HF with preserved ejection fraction (based on the HFA‐PEFF score); and they had to meet at least one criterion of the following indicating functional limitation: ≥6 s to walk 4 m, inability to wash ≥3 days of the last 7 days, or symptoms of dyspnoea at rest. Enrolment ended 30 January 2025; 93 patients completed randomization. The primary endpoint is a hierarchical composite (analysed by win ratio): (1) days alive and able to wash, (2) 4 m walking ability, and (3) patient global assessment of well‐being.

**Conclusions:**

EMPATICC evaluates whether HF therapy can improve function and well‐being in advanced cancer, potentially reshaping care in this population.

## Introduction

In the United States, approximately 17 million individuals were diagnosed with cancer as of 2021.^1^ In Europe, the five‐year prevalence is estimated to be 14 million.^2^ Nearly half of these patients cannot be cured and eventually progress to end‐stage palliative disease. As cancer advances, patients increasingly depend on others for assistance with basic daily activities. Maintaining functional self‐care is critical for preserving patient autonomy and enhancing quality of life, serving as a cornerstone of self‐management and overall well‐being.^3^ Functional self‐care, including personal hygiene and short‐distance walking is closely tied to physical performance and general health status.

End‐stage cancer is associated with systemic pathophysiological changes that contribute to a decline in physical function. Tumour progression, inflammation, metabolic dysregulation, and treatment‐related toxicities contribute to multi‐organ dysfunction, including cardiovascular impairment.^4^, ^5^ Chronic inflammation and oxidative stress drive structural cardiac changes such as fibrosis and apoptosis, which contribute to myocardial atrophy and dysfunction.^6^ In this context, general cachexia—as a syndrome that is marked by weight loss, cardiac muscle wasting, and metabolic abnormalities—is a major contributor to heart failure (HF) symptoms in cancer patients.^7^ These pathophysiological changes manifest as a distinct cancer‐disease‐like phenotype characterized by cardiac dysfunction, and disruptions in homeostatic processes. Studies indicate that cardiac wasting is present in up to 50% of patients with end‐stage cancer, contributing significantly to symptoms such as dyspnoea, congestion, and severely diminished physical function.^6^ Cardiovascular complications account for up to 30% of mortality in advanced stage cancer patients, underscoring the critical need to address cardiac dysfunction in this group.^7^, ^8^ While pharmacological HF medicines have been proposed to mitigate cachexia and provide benefits in cardiac wasting, targeted approaches to reduce the cardiovascular sequelae of advanced cancer remain largely underexplored.^9^, ^10^, ^11^, ^12^

The optimization of HF therapy in cancer patients may result in beneficial outcomes that could range from mitigation of cardiac wasting to an improvement in overall fitness and preservation of functional self‐care and independence.^13^, ^14^ Most cardio‐oncology trials to date have focused on managing cancer therapy‐related cardiotoxicity, particularly from anthracyclines or HER2‐targeted therapies. However, no randomized studies have specifically addressed the mechanisms driving cardiac dysfunction and dyspnoea in end‐stage cancer patients. Herein, we describe the rationale and design of the EMPATICC (EMPower the heArt of patients with TermInal Cancer using Cardiac medicines) trial, which is a randomized clinical study designed to evaluate the safety and efficacy of optimized HF therapy in patients with end‐stage cancer at risk of cardiac wasting. This trial investigates a regimen comprising of sacubitril/valsartan, empagliflozin, ivabradine, and ferric carboxymaltose (FCM), combined with usual care, to improve self‐care ability, quality of life and clinical symptoms among patients with terminal cancer in the palliative care population.

## Methods

### Study design

The EMPATICC study is a multicentre, investigator‐initiated, randomized, controlled, double‐blind proof‐of‐concept trial. We aimed to enrol 72–108 patients across five centres in Germany. Participants were randomly assigned in a 1:1 ratio to either an intervention arm or a control arm in a blinded manner (*Graphical Abstract*). Patients in the intervention arm received optimized HF therapy, including sacubitril/valsartan, empagliflozin, ivabradine, FCM, and optimal usual care. Those in the control arm will receive only the optimized usual standard of care. To keep blinding of therapy for patients and caring medical staff, treatment decision initially and during the trial were made by unblinded study investigators who otherwise were not involved in patient care or study assessments. The latter was all performed by blinded study investigators.

The trial consists of a 30‐day randomized phase followed by a 30‐day open‐label extension phase, during which all participants will receive the optimized therapy (*Figure* *1*). The extension phase aims to ensure that all study participants receive active treatment and to gather additional data on the safety of optimized HF therapy in this vulnerable population. This trial adheres to the principles of Good Clinical Practice and the Declaration of Helsinki.^15^, ^16^ All relevant institutional review boards approved the protocol. Universitätsmedizin Essen, Germany, is the trial sponsor, with support from an unrestricted grant from the BROST Stiftung.

**Figure 1 ejhf3799-fig-0001:**
[figure not shown]
Schematic overview of the chronological structure of the trial. Intervention phase: 30‐day double‐blind randomized therapy. The intervention involved an optimized heart failure treatment regimen, including sacubitril/valsartan, empagliflozin, ivabradine, and intravenous ferric carboxymaltose. Extension phase: 30‐day open‐label therapy.

### Patient population

Eligible participants include adults aged 18 years or older with stage 4 solid cancer under palliative care, an expected survival time of 1–6 months, and optimized pain management. Patients must fulfill at least two criteria indicating cardiovascular risk (resting heart rate >70 bpm, N‐terminal pro‐B‐type natriuretic peptide [NT‐proBNP] ≥600 pg/ml, elevated high‐sensitivity troponin [>99th percentile], left ventricular ejection fraction [LVEF] <55%, left ventricular [LV] mass reduction >15% since cancer diagnosis, or iron deficiency with transferrin saturation [TSAT] <20%), or moderate/high likelihood of HF with preserved ejection fraction based on the HFA‐PEFF score and at least one functional or symptomatic criterion must be present. These functional and symptomatic criteria include a time taken ≥6.0 s to walk 4 m or the inability to walk 4 m, the inability to wash themselves for at least 3 days of the last 7 days, or the presence of shortness of breath at rest (New York Heart Association [NYHA] class IV symptoms). These pre‐randomization eligibility domains were intended to ensure that included patients exhibit both signs of HF progression and clinical frailty. LV mass reduction was assessed using echocardiography. The detailed eligibility criteria are shown in *Table* *1*.

**Table 1 ejhf3799-tbl-0001:** Inclusion and exclusion criteria of the EMPATICC trial

**Inclusion criteria**
1. Signed and dated informed consent obtained before any trial‐related activities. Trial‐related activities are any procedures that would not have been done during normal management of the subject.
2. Age ≥18 years
3. Male or female subject with solid cancer in UICC stage 4 (in palliative care)
4. One to six months expected survival as assessed according to local standards
5. Patients under optimized pain management
6. Patients must be able to swallow tablets
**Group 1 criteria for inclusion (at least two need to be met):**
7. Heart rate at rest >70 bpm
8. NT‐proBNP ≥600 pg/ml
9. Elevated troponin (>99th percentile of the respective high‐sensitivity test)
10. LVEF <55%
11. HFpEF likelihood medium or large based on the HFA‐PEFF score (≥50% probability)
12. Evidence of LV mass reduction >15% since the start of cancer
13. Iron deficiency with TSAT <20%
**Group 2 criteria for inclusion (at least one needs to be met):**
14. 4 m gait speed ≥6.0 s for 4 m or not able to walk 4 m at all
15. Not being able to wash themselves in at least 3 of the last 7 days
16. Presence of shortness of breath at rest (NYHA class IV)
**Requirement for inclusion:**
Fulfilled criteria 1–6 and at least two met criteria of Group 1 PLUS
at least one met criterion of Group 2.
**Exclusion criteria**
1. Ongoing haemodialysis
2. Patients currently on intravenous iron
3. Acute sepsis with at least 2 points at the qSOFA score.^17^ The use of intravenous antibiotics is permitted in patients with a lower qSOFA score.
4. Ongoing acute exacerbation of COPD
5. Acute STEMI or severe PE or severe DVT (currently or in last 4 weeks)
6. Current uncontrolled cerebral metastasis
7. Impaired neurological status, precluding the ability to walk
8. Unable or unwilling to give written informed consent
9. Participation in other interventional trials using investigational products in randomized settings within the last 30 days

COPD, chronic obstructive pulmonary disease; DVT, deep vein thrombosis; HFpEF, heart failure with preserved ejection fraction; LV, left ventricular; LVEF, left ventricular ejection fraction; NT‐proBNP, N‐terminal pro‐B‐type natriuretic peptide; NYHA, New York Heart Association; PE, pulmonary embolism; qSOFA, Quick Sequential Organ Failure Assessment; STEMI, ST‐elevation myocardial infarction; TSAT, transferrin saturation; UICC, Union for International Cancer Control.

### Screening and enrolment

Data collection details are summarized in *Table* *2*. Screening will begin upon obtaining informed consent, with each participant assigned a unique screening number incorporating a site‐specific identifier. During screening, compliance with inclusion and exclusion criteria will be evaluated. Screening failures will be documented in the trial database, including reasons for non‐eligibility. If minor deviations from the criteria occur and the clinical status of a patient changes, one re‐screening may be permitted. Eligible participants meeting all criteria will proceed to randomization and intervention. The trial aimed to include 72–108 participants. To account for potential dropouts before the 30‐day intervention phase, the Steering Committee may decide to enrol additional participants. Mortality is a key safety outcome. Therefore, patients who die before completing the intervention phase will not be classified as ‘dropouts’. The total enrolment was planned to not exceed 108 participants. The trial ended on 30 January 2025. The final number of patients with complete randomization was 93.

**Table 2 ejhf3799-tbl-0002:** Trial flow chart

Description	Screening phase	Baseline	Intervention phase			Extension phase			
			Day 1 to 30			Day 31 to 60			
Timing	1–3 days before baseline		±2 days			±2 days			
Day(s)	−3 to −1	1^a^	10	20	30	31	40	50	60
Informed consent	X^b^								
Inclusion/exclusion criteria	X								
Demographic data	X								
Concomitant illness and medical history^c^	X								
Weight, height	X^d^	X^e^			X^e^				X^e^
Vital signs^f^	X^d^	X	X	X	X		X	X	X
ECG	X^d^		X	X	X		X	X	X
4 m walking test^g^	X	X	X	X	X		X	X	X
Laboratory tests^h^	X^d^	X	X		X		X		X
Echocardiography	X^d^				X				X
Performance status and QoL questionnaires^i^		X	X		X		X		X
PGA			X	X	X		X	X	X
Adverse event reporting^j^								
Randomization		X^a^							
Study treatment (optimized HF therapy/placebo)		X^k^			X				
Study treatment (HF therapy/care)						X^l^			X
Recording of changes in concomitant medication^m^	X								

ECG, electrocardiogram; HF, heart failure; PGA, patient global assessment; QoL, quality of life.

^a^
Baseline assessments will be done in the morning. Randomization will be done, and study medication will be administered immediately after completion of baseline assessments.

^b^
Informed consent has to be signed (with date and time) before any trial‐related activity.

^c^
Including, but not limited to Union for International Cancer Control stage, expected survival time as assessed according to local standards, pain management, chronic obstructive pulmonary disease status, shortness of breath (New York Heart Association class IV), cerebral metastasis, neurological status, sepsis assessment (Quick Sequential Organ Failure Assessment), deep vein thrombosis, pulmonary embolism, tumour aetiology.

^d^
Assessments done within the last 7 days before screening for which results are available do not have to be repeated. Screening ECG and echocardiography will be used for baseline assessment.

^e^
Weight only.

^f^
Blood pressure and pulse rate.

^g^
Test for walking ability and speed. The speed of patients not being able to walk 4 m will be set to zero.

^h^
N‐terminal pro‐B‐type natriuretic peptide, high‐sensitivity troponin T/I, iron, transferrin, blood cell count, haemoglobin (g/dl), transferrin saturation (%), C‐reactive protein (mg/dl), electrolytes (potassium, sodium, chloride), creatinine, estimated glomerular filtration rate, glucose, additional sample for later analysis, particularly of cardiovascular and metabolic biomarkers. Blood loss will be about 30 ml per sampling.

^i^
To be filled out by subject (with or without help from physician): EORTC QLQ‐C15‐PAL (European Organization for Research and Treatment of Cancer Quality of Life Questionnaire‐Core 15‐Palliative Care) (on days with patient global assessment [PGA], PGA will be answered first). To be filled out by physician in the given order: Eastern Cooperative Oncology Group Performance Status, Karnofsky Performance Status, Palliative Performance Scale, Palliative Prognostic Index, Palliative Prognostic Score.

^j^
Adverse events will be reported from randomization until the last visit.

^k^
Optimized HF therapy or placebo will be administered from day 1 to day 30.

^l^
Optimized HF therapy will be administered to all patients from day 31 to day 60.

^m^
Changes in concomitant medication from screening will be recorded from baseline until the last visit of each individual. Only newly started or stopped medication will be documented. Dose changes will not be documented.

### Medication and procedures

Each medication in the optimized HF treatment regimen will be administered according to approved guidelines and dosages, as detailed in online supplementary *Table* *S1*. Patients with contraindications to specific treatments will be excluded. This trial includes both blinded and unblinded teams. The blinded study team, including investigators assessing outcomes and patients receiving treatment, remained unaware of group allocation, while the unblinded study team managed treatment administration without disclosing allocations. Sacubitril/valsartan therapy will be initiated at 24/26 mg twice daily. The unblinded team will determine the target dose, up to a maximum of 97/103 mg twice daily. Patients currently on angiotensin‐converting enzyme inhibitors or angiotensin receptor blockers will be transitioned to sacubitril/valsartan. Ivabradine will be prescribed to patients with a resting heart rate ≥75 bpm in sinus rhythm. Ivabradine will be started at 5 mg twice daily. Dosing adjustments, up to a maximum of 7.5 mg twice daily, will be made at the discretion of the unblinded cardiology team. Patients with iron deficiency (TSAT <20%) will receive intravenous FCM.^18^ Iron dosage will be calculated based on body weight and haemoglobin levels, as outlined in online supplementary *Table* *S2*. FCM will be administered in 0.9% sodium chloride solution, with single doses not exceeding 20 mg iron/kg body weight or 1000 mg iron. For doses above 1000 mg, the remaining dose will be administered 1 week after the initial infusion. Empagliflozin will be administered at a standard dose of 10 mg once daily. Patients with significant renal or hepatic insufficiency will be excluded from receiving this medication. All investigational medicinal products used in this trial are pre‐approved and sourced from the national market.

All medications will be administered by the unblinded study team, with certified cardiologists at each site overseeing dosing decisions. Patients in the control group will receive one to three placebo pills and/or saline infusions to maintain blinding (placebo pills: ‘P‐Tabletten blau’, Lichtenstein, ‘P‐Tabletten weiss 8 mm’, Lichtenstein, and ‘P‐Dragees rosa’, Lichtenstein – all manufactured by Zentiva Pharma, Berlin, Germany). Physiological saline solution will serve as the placebo for FCM. To ensure blinding, saline and FCM infusions will use black infusion sets wrapped in opaque foil. Following the extension phase of the trial, treatment regimens for surviving patients will be communicated to their palliative care oncologists, who will determine ongoing therapy in consultation with the patients.

The selection of therapies was guided by prior clinical experience in this vulnerable population, with the focus on maintaining tolerability while addressing key pathophysiological targets. Empagliflozin was included based on robust evidence of benefit across the ejection fraction spectrum, with its additional beneficial effects on systemic inflammation and general cardio‐renal‐metabolic status.^19^ Sacubitril/valsartan was included in the treatment regimen due to its demonstrated benefits in improving cardiac function and promoting reverse remodelling in HF patients specifically as well as in cancer patients with HF regardless of ejection fraction.^20^ Multiple studies have demonstrated that sacubitril/valsartan improves echocardiographic measures such as LVEF and reduces NT‐proBNP concentrations in this population.^21^ Studies have shown elevated resting heart rate is independently associated with increased risk of all‐cause and cancer‐specific mortality.^22^, ^23^ Ivabradine was added due to its ability to reduce resting heart rate without lowering blood pressure. Ivabradine has also shown to reduce anthracycline‐induced cardiotoxicity and improve cardiac haemodynamics in patients with advanced cancer.^24^ FCM was included to address functional iron deficiency, which is highly prevalent in both HF and cancer‐related cachexia.^25^ We expect it to contribute to improvements in functional status in the short term. Given the high prevalence of frailty and hypotension in patients with advanced cancer and cardiac cachexia, beta‐blockers and mineralocorticoid receptor antagonists were not included in the treatment regimen. Furthermore, there were clinical concerns that beta‐blockers—particularly in the short term—would adversely impact on quality of life and symptom status in these vulnerable patients.^26^, ^27^ There was also a strong desire to avoid any possible risk of hyperkalaemia.^28^ Hence, in this first trial, mineralocorticoid receptor antagonists were avoided.

### Study visits and follow‐up

Eligible patients will be randomized in a 1:1 ratio to one of two treatment groups: with standardized scheme of HF care including up to four different drugs or standard of care. Randomization will occur on day 1, marking the start of the 30‐day randomized phase. Patients will undergo in‐person assessments on days 10, 20, and 30 (*Table* *2*). Following this, all participants will transition into a 30‐day open‐label extension phase to receive optimized HF therapy. Assessments in the extension phase will be conducted on days 40, 50, and 60 (*Table* *2*). Study discontinuation may occur due to safety concerns, including clinical abnormalities or significant adverse events, such as allergic reactions or diabetic ketoacidosis. All patients are informed at the beginning of the study about the potential for reassessments during the trial. This approach ensures rigorous follow‐up and comprehensive monitoring throughout the study period. The trial will conclude with a final assessment at day 60 or earlier if discontinuation occurs.

### Primary endpoint

The primary efficacy objective of this study is to assess the impact of optimized HF therapy on self‐care ability and self‐reported health status in terminal cancer patients receiving palliative care. The primary hierarchical endpoint (to be analysed by the win ratio) has the following components: (1) days alive and being able to wash themselves, (2) the ability to walk 4 m, and (3) the self‐reported patient global assessment (PGA) of subjective well‐being during 30‐day period to the end of placebo‐controlled phase.

For the first component ‘days alive and being able to wash themselves’, any method for washing (shower, bath, sink, or sponge bath in bed) will be considered during the 30‐day period to the end of the placebo‐controlled phase (up to the visit of day 30 [30 ± 2 days after the baseline visit]), with the counts ranging from 0 to 32 days. A higher number (or higher proportion) of days will determine the ‘win’, if the difference between two patients being compared exceeds 1 day (or an equivalent proportion). For cases when both patients survive the entire placebo‐controlled phase, then only the period of time of the patient with shorter observation time will be considered (i.e. day 28–32 or the related visit). If only one of the two patients compared reached the final assessment day and the withdrawal of the second patient is considered independent of disease severity (in blinded assessment), the shared observation time (i.e. to the end of study for the patient with shorter observation time) is considered. If only one of the two patients compared reached the final assessment day and the withdrawal of the second patient is considered dependent on disease severity, this person is considered unable to wash themselves, to not being able to walk, and to consider their health ‘much worse’ in PGA until the end of study (i.e. the visit on day 30).

If neither of the patients complete their study period (due disease progression [i.e. entering the dying process] or death), an imputed observation time (day 30) will be used to assess the outcome for both patients. For patients with documented disease progression related study withdrawal, a worst‐case imputation will be performed, i.e. patients will be considered unable to wash themselves, unable to walk, or considered their health ‘much worse’ in the PGA. If precise day‐by‐day recorded data are not available for both patients, and results for the observation period are only provided as summary statistics at visit‐day 10, visit‐day 20, and visit‐day 30, then results will be calculated up to the end of their last common visit on day 10, 20, or 30, respectively, using the ‘last common visit’ approach. Under the ‘last common visit’ approach, the win criterion for the percentage of days alive and able to wash oneself is defined as a difference between two patients of >15.00% for an observation period extending to visit‐day 10, >10.00% for visit‐day 20, or >5.00% for visit‐day 30, with the patient demonstrating the higher percentage deemed the winner.

The second endpoint component, i.e. the ‘ability to walk 4 m’ (during 30‐day intervention phase), will be assessed at days 10, 20, and 30, with counts ranging from 0 to 3 visits. The patient with a higher number will be the ‘winner’. The walking ability is measured by the time taken to walk 4 m, with timing starting from the first foot movement and ending when one foot crosses the finishing line. The result is also used to calculate walking speed. For patients who die or are unable to walk, the walking speed will be recorded as zero.

The third component of the primary endpoint, i.e. ‘self‐reported PGA of subjective well‐being’, will be assessed at the last common assessment visit where both patients were alive (i.e. day 30, 20, or 10). The PGA assesses overall well‐being since enrolment on a 7‐point Likert scale ranging from ‘much worse’ to ‘much improved’. For patients who died, a value (8) ‘dead’ will be assigned. A better PGA score will be considered a ‘win’ but only if it is better than at least score of 6 (i.e. a patient needs to at least ‘moderately worse’). Pre‐specified sensitivity analyses for this win ratio include introducing all‐cause mortality as the highest‐priority component, where longer survival wins with a difference exceeding one day, and reversing the order of walking and PGA components.

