**Primary endpoint (assessed in the controlled treatment phase)**
Win ratio hierarchical endpoint:
Days alive and able to wash themselves since baseline during 30 days of follow‐up to the end of the placebo‐controlled phase, with counts ranging from 0 to 32 days.^a^, ^b^
*Note 1: Definition of ‘washing themselves’: patient performed act of washing by themselves without interference of staff, regardless of whether as shower or bath, on a sink, or using a ‘sponge bath’ in the bed*.
*Note 2: Higher number of days (or proportion of days) will be counted as win, if the difference is >1 day (or a equivalent proportion)*.
2 Number of days alive and able to walk 4 m, assessed up to three times (days 10, 20, and 30), with counts ranging from 0 to 3 days.
*Note 1: Walking ability and time are assessed starting in a still standing position – timing starts with the first foot movement and ends when one foot completely crosses the 4 m‐finishing line. Times are used to calculate walking speed (see also other secondary endpoints). If a patient has not completed the 4 m walking distance within 60 s, the patient is considered not being able to walk 4 m and the related speed is set at zero*.
*Note 2: Higher number of days will be counted as win*.
3 PGA of well‐being during the 30‐day period to the end of the placebo‐controlled phase (7‐point Likert scale).
*Note: Better PGA score counts as win, but only if the winning score is better than ‘much worse’*.

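### The visit-summary fallback for washing days can cut a pair before a death, has no stated rank against the death and withdrawal imputation, and uses different win thresholds from the daily rule

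*Protocol article*

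**What the plan says.** In the protocol article, Primary endpoint, the first tier counts days alive and able to wash up to the day-30 visit, "with the counts ranging from 0 to 32 days". Table 3 lists the same variable ("Days alive and able to wash themselves since baseline during 30 days"). With daily data, a difference of more than 1 day, or an equivalent proportion, wins.

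A fallback follows. Its condition is "If precise day‐by‐day recorded data are not available for both patients", and it applies where "results for the observation period are only provided as summary statistics" at visits 10, 20 and 30. The pair is then evaluated only up to its last common visit. A win needs a difference in the percentage of days of more than 15% at day 10, 10% at day 20 or 5% at day 30. The Statistical analysis section uses win criteria for aggregated washing data again for washing days as a key secondary endpoint.

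The same section also gives imputation rules:
- A severity-related withdrawal, compared with a completer, counts as unable to wash until day 30.
- A withdrawal unrelated to severity limits the pair to shared time.
- If neither patient completes, because of progression or death, day 30 is imputed for both.

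No sentence ranks these rules against the fallback, and none explicitly covers a completer compared with a patient who died.

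Screening and enrolment says "Data collection details are summarized in" Table 2. That table has rows for the walk and the patient global assessment (PGA), but none for washing. Its footnote on physician-completed scales names "Eastern Cooperative Oncology Group Performance Status, Karnofsky Performance Status, Palliative Performance Scale, Palliative Prognostic Index, Palliative Prognostic Score" and no washing record. The table therefore does not show which form of washing data is collected.

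**The concern.** Washing days decide each pair first, carry the main sample size calculation and are the first key secondary hypothesis tested. The result of a pair should depend on the two patients and not on how their days were written down. Under the text as it stands, the same two histories can give a different winner, or a tie instead of a win, according to the data form.

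The more serious effect is at death. The endpoint counts days alive, so every day after a death is known to be zero. A cut at the last common visit sets those known zeros aside, together with the survivor's later washing days. This happens in the primary analysis of a population with an expected survival of 1 to 6 months.

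**Working it through.** **The plan's own figures.** Sample size calculation assumes 58 completers, a difference of 5 days, SD 6 and a probabilistic index of 0.278. Noether's formula gives Φ(√(12 × 0.25 × 58) × |0.278 − 0.5| − 1.96) = Φ(13.19 × 0.222 − 1.96) = 83%, in line with the stated 83.4% to 86.4%. For a win ratio of 2.1 with 10% ties, the Yu–Ganju formula gives N = [4 × 1.1 / (3 × 0.25 × 0.9)] × (1.96 + 0.842)² / (ln 2.1)² = 92.9, in line with 46 per group. Both reproduce. Neither depends on how washing is recorded, so the power figures are not in dispute.

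**1. A pair in which the cut changes the winner.** Both patients have summaries only, so the fallback applies on any reading of its condition.
- Patient A washes on 10 of 10 days and dies on day 19, before a day-20 visit. A's washing on days 11 to 19 is not recorded.
- Patient B washes on 8 of 10 days, then every day to day 30.
- Cut at day 10: 100% − 80% = 20 points, which exceeds 15. A, who died, wins.
- Counted to day 30: B has 8 + 20 = 28 days. A has between 10 and 19, because days 11 to 19 are unknown and days 20 to 30 are zero. B leads by at least 9 days and wins.

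B wins whatever happened on A's unrecorded days. The reversal comes from the rule and not from a gap in the data.

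**2. Thresholds in days.** The percentages are read as percentage points of the observation period.

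| Cut at | Threshold | In days | Whole days needed | Daily rule (>1 day) | 1 day as % |
|---|---|---|---|---|---|
| Day 10 | >15% | >1.5 | 2 | 2 | 10% |
| Day 20 | >10% | >2.0 | 3 | 2 | 5% |
| Day 30 | >5% | >1.5 | 2 | 2 | 3.3% |

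In whole days only the day-20 rule differs. A 2-day difference is exactly 10%, so it ties under the fallback and passes to the walking tier. With daily data it wins.

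**3. The trigger.** The condition can mean that neither patient has daily records, or that not both have them. If a fraction f of patients has summaries only, the share of pairs entering the fallback is f² on the first reading and 1 − (1 − f)² on the second. At f = 30% (an assumption) this is 9% or 51%.

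**4. How much observation time could be lost.** Entering the fallback is not the same as losing data, because two patients who both reach day 30 keep the whole window. Let q be the proportion not completing, spread evenly over days 1–10, 11–20 and 21–30, with patients independent and no imputation applied. The share of pairs with a last common visit at day 10 or none is 1 − (1 − 2q/3)².

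| q | All patients summary-only | f = 30%, one such patient triggers | f = 30%, both needed |
|---|---|---|---|
| 20% | 24.9% | 12.7% | 2.2% |
| 40% | 46.2% | 23.6% | 4.2% |

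At q = 20%, 0.8² = 64% of pairs reach day 30. The 20% is the plan's dropout figure. Deaths are not classed as dropouts and would add to it, but no death rate is given, so 40% is illustrative.

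**The case against.** The fallback is a conditional rule for missing daily data. It does not show that summaries were ever used, or how often. A journal article may leave the diary or case report form to the full protocol, so a missing row in Table 2 is not in itself a fault. The plan also has safeguards. Severity-related withdrawals are scored as unable to wash, day 30 is imputed when neither patient completes, and Statistical analysis says that deceased patients are imputed. A sensitivity analysis puts all-cause mortality first and would give the pair above to the survivor. With a visit window of ±2 days, the day-20 visit could also fall on day 18, before a death on day 19.

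Most of this stands, and it limits the point. A reader might infer that many pairs lose most of their washing data. The documents do not support that: loss needs both the fallback and a non-completer, and neither frequency is given. Nor do they support the inference that the data form follows care setting or illness.

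The safeguards do not close the gap in the primary analysis. No rule puts imputation ahead of the cut, and the general statement on deaths offers a worst-case value or the last observation carried forward without saying which applies here. The mortality-first analysis is only a sensitivity analysis. The visit window changes when the example arises, but a death can still precede the visit.

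**Conclusion.** The point holds as a defect in a stated rule. For the first tier of the primary endpoint, the plan accepts two data forms with different windows and, at day 20, a different effective threshold. It does not say whether the last-common-visit cut or the imputation for death and withdrawal prevails. If the cut prevails, a patient who died can beat a survivor who leads by at least 9 days over the 30-day period.

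The extent is unknown. It depends on the share of patients with summaries only, on the 30-day death rate and on how the trigger is read. The ranges above rest on assumed values for the summary-only share and for the timing of non-completion. They show that the effect could be small or material, not which it is.

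**What to change.** Before database lock, and blinded to allocation:

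1. Close each washing record to the day of death or disease-related withdrawal, from existing ward or caregiver records where available.
2. Count all later days to day 30 as not able to wash, whichever data form is used, and state that this takes precedence over the cut at the last common visit.
3. Use the fallback only for days that cannot be recovered.
4. State whether its condition means that neither patient, or not both patients, has daily records.
5. Report the share of pairs decided under the fallback. Add a sensitivity analysis that scores unrecoverable days first all as washed and then none as washed.

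The cost is some record review and a few sentences in the plan. Records may be less complete for patients cared for at home, which the sensitivity analysis would expose. Enrolment has ended, so a new daily diary or baseline field is not proposed.
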